**Table 1 Tab1:**
[figure not shown]
Schedule of enrolment, interventions, and assessments

The controlled study has three different arms. In the case of schools, we cluster-randomized participants to one of two conditions: (A) intervention schools or (B) waiting list or control schools. Randomization has been done at school level. Thereafter, the baseline measurements were performed in both conditions, and, after that, the intervention group began its activities, and measurements were taken as described above (Table 1). One year after the baseline measurement intervention group (A), the waiting list group began its program. Measurements are finally to be made a year later.

In the case of Junis’s groups, it was not feasible to do a cluster randomization at the managerial level as the involvement of local chapters was more difficult to achieve. The groups will be led by regular Junis volunteers.

As for the social services group, we will have the same arrangement, but no waiting-list control condition. Here, a new round of groups is planned for the second year. On the other hand, we will have a follow-up measurement of the first wave’s intervention groups in year 3 for both the Junis and the social services groups. The groups will be run by social workers.

However, it will be possible to compare developments in these two study arms with the data collected in the control schools.

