### Participants and recruitment

A calculation of statistical power has been made for the interventions. For the universal intervention, there is an effect size of d = 0.3 and a power of 0.8, and the corresponding statistics are expected to test a group size of 176 in each group. The recruitment of schools for the evaluation of RESCUR has been completed. These schools have been recruited from different parts of Sweden, and in both urban and rural areas. There are 8 intervention schools in five municipalities, including 10 classes in school year 1, and 8 classes in school year 4. The intervention group includes 394 children. There are 9 school in the waiting list control schools in six municipalities, including 10 classes in school year 1, and 9 classes in school year 4. The waiting list controls include 401 children. The number of classes in which RESCUR is carried out in the municipalities is larger than necessary to carry out the project based on an evaluation or “power perspective”. Oversampling, however, is a common and good strategy to deal with any delays, etc. from the project, and thus to reduce threats to the implementation of the project. Participants are randomized to the intervention and waiting list/ control groups based on residence and school. The planned survey is regarded as having adequate statistical strength.

The project group has trained 23 teachers in the intervention schools. In March 2018, 20 teachers in the waiting list control schools will be trained in the RESCUR intervention.

A power analysis for the interventions in social services and the NGO has been performed. For the selective groups, an effect size of d = 0.5 and power of 0.8 is calculated, which results in a double-sided statistical testing of group differences (alpha = 0.05), and a group size of 64 children in each of the two groups. The planned size allows for a certain amount of dropout in the study.

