Recruitment for the evaluation of RESCUR in the social services groups is ongoing. At present, several social-services units have expressed an interest in being included in the evaluation. We will recruit participants to 8 groups with approximately eight participants for the first year. Here, there will be no randomization, but a second round of groups is scheduled for the second year. It provides a total of 128 children over the 2 years. The planned size of the sample in social services is less, since previous research has clearly shown that interventions in targeted or selected groups have a significantly higher effect size than those in universal groups (i.e., the school). The age of participants in the social services groups will be 7–9 and 9–12 years. During 2017, RESCUR groups have started in social services in five municipalities, including 42 children. Fifteen group leaders from six municipalities have received the RESCUR training so far.

For groups within Junis, 22 leaders from ten different districts have been asked to participate. We plan to have a total of 16 groups of approximately 8 participants in the Junis group. It provides 128 participants. The age of the participants will be between 7 and 12 years. Eight Junis leaders from 5 municipalities have been trained, but so far only one group has started to use the RESCUR intervention.

An important question to answer in the project is how the recruitment of participating actors as well as children is facilitated in the three types of organization. Another important question is whether the RESCUR method works equally well for children in the three types of organizations.

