### Data management and analysis

All collected material from surveys, observations and interviews will be encoded before analysis. The code key, with the researcher’s name and code number, will be stored separately in fireproof locked cabinets, which only research director [name] has access to. All collected material will be stored for at least 10 years in other fireproof archives, as required by law. All primary data will be stored at Göteborg University. Because the project has a longitudinal design, the research participants are not anonymous. However, it is of the utmost importance that the principle of confidentiality is followed. The names, addresses or the like of the children, parents or co-workers will not be read-in without being treated confidentially and only for this project. The results are only reported at group level, which means that individuals cannot be identified.

The research group has monthly meetings together with the implementing organization in order to facilitate the smooth running of the intervention study. In order to answer the five research questions, both quantitative and qualitative analyses will be applied in this intervention study, which uses a mixed methods research approach. The quantitative data will be managed using SPSS as a tool for analysis. In the randomized trial, we will use latent change models to examine the changes in child outcomes over time. To obtain unbiased estimates despite attrition, we will employ intention-to-treat analysis. Cohen’s *d* effect sizes were computed to estimate the effects of the programs compared with the wait-list condition while taking the initial level of each outcome measure into account. The social services and the NGO groups will be compared with controls matched from the waiting list controls. Mediating and moderating factors will be analyzed with regard to the primary outcomes.

The interviews will be transcribed and analyzed by qualitative content analysis. All sources of data will be used in the implementation study, where the inferences will be drawn using mixed-methods procedures.

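### The 64-per-group figure for the social-services and Junis arms assumes independent children, although treatment is given in groups of about eight; restate it, and name the variance method for the matched comparison

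*Protocol article*

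**What the plan says.** **Sizing.** Participants and recruitment reports a power analysis for the social-services and NGO interventions: "For the selective groups, an effect size of d = 0.5 and power of 0.8 is calculated", two-sided at alpha 0.05, leading to "a group size of 64 children in each of the two groups". It gives no ICC, design effect or group size. It adds that "The planned size allows for a certain amount of dropout in the study", without a rate.

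**Delivery.** For social services: "We will recruit participants to 8 groups with approximately eight participants for the first year". A second round in year 2 brings the planned total to 128. For Junis: "We plan to have a total of 16 groups of approximately 8 participants in the Junis group", also 128 children. In the Design section, after Table 1, social workers run the social-services groups, and for Junis "The groups will be led by regular Junis volunteers".

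**Controls.** Neither arm has a randomised control group of its own. Data management and analysis states: "The social services and the NGO groups will be compared with controls matched from the waiting list controls". That pool is 401 children in 19 classes in 9 schools. The same section names latent change models, but for the randomised trial. It gives no model, unit of analysis or standard error for the matched comparison.

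**The concern.** Children in one RESCUR group share sessions, leadership and each other, so their outcomes are likely to be correlated. The protocol itself expects delivery to matter: the Design section says poor implementation leads to poor or no results, and the implementation study measures fidelity and quality of delivery for that reason. In Junis the leaders also complete the adult ratings (Reports from adults), so a lenient or severe rater would shift the adult-reported outcomes of a whole group.

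This clustering is separate from the randomisation of schools. It arises from group delivery on the treated side. These children are not analysed as members of trial schools, so a school term in the randomised comparison would not cover it.

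Two things are at stake. The printed power of 0.8 at 64 per group does not describe 64 children treated in eight groups. And if the same independence were carried into the matched comparison, differences between groups or leaders could pass for a programme effect. The effect sizes from these arms also feed research question 5, which compares the universal, selective and indicative levels.

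**Working it through.** **Inputs from the protocol:** d = 0.5, power 0.8, two-sided alpha 0.05, 64 per group; groups of about 8; 8 social-services groups in year 1; 128 planned per arm (128 / 8 = 16 groups); 401 controls in 19 classes in 9 schools.

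**Assumptions:** ICC of 0.05 / 0.10 / 0.15 within RESCUR groups (the protocol gives none); SD = 1; 1:1 matching; no dropout; controls independent unless stated.

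**1. Reproduce the plan's figure.** A two-sample t-test at these inputs needs 63.77 per group, so 64, and its power at 64 v 64 is 0.801. The figure corresponds to a design effect of 1 with no dropout allowance.

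**2. Design effect on the treated side.** DE = 1 + (8 − 1) × ICC = 1.35 / 1.70 / 2.05.

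**3. Power with group delivery.** Var = DE/n_T + 1/n_C, with Satterthwaite degrees of freedom (number of groups − 1 on the treated side, n_C − 1 on the control side) and the noncentral t. Worked case, 64 v 64 at ICC 0.05: Var = 1.35/64 + 1/64 = 0.0367; SE = 0.192; noncentrality 0.5/0.1916 = 2.61; df = 20; power 0.70.

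| ICC | DE | Power, 64 v 64 (8 groups) | Power, 128 v 128 (16 groups) |
|---|---|---|---|
| 0 | 1.00 | 0.80 | 0.98 |
| 0.05 | 1.35 | 0.70 | 0.95 |
| 0.10 | 1.70 | 0.63 | 0.92 |
| 0.15 | 2.05 | 0.57 | 0.88 |

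A normal approximation gives 0.74 / 0.68 / 0.63 at 64 v 64. The difference is the penalty for having only eight treated groups.

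**4. If the analysis ignored groups.** At equal sizes, true SE / naive SE = √((DE + 1)/2) = √1.175 / √1.35 / √1.525 = 1.08 / 1.16 / 1.23. The true error rate of a nominal 5% test is 2 × [1 − Φ(1.96 / ratio)] = 7.1% / 9.2% / 11.3%. The ratio does not depend on n, so it is the same at 64 v 64 and 128 v 128: recruiting more groups of eight restores power but not the error rate.

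**5. If controls are clustered too.** As an illustration, 128 matched controls spread over 19 classes are 128/19 = 6.7 per class, close to the treated group size. With the same DE on both sides, the error rate of a test ignoring clustering is about 9% / 13% / 17%. Power at 128 v 128, by the normal approximation, is 0.93 / 0.87 / 0.80. On this assumption 128 per arm absorbs an ICC up to (128/64 − 1)/7 = 0.14.

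**The case against.** A reader might infer that the reported intervals for these arms will be too narrow. The protocol does not say so. Data management and analysis is silent on the model and variance for the matched comparison, and a journal protocol commonly leaves that to an analysis plan, which is not at hand. Silence is not a choice of independence, so the error-rate figures stand only as a conditional. What makes the condition worth stating is that the one statistical figure printed for these arms does assume independence.

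A reader might also infer that these arms are underpowered. At the planned size that is not shown. The 64 is a calculated minimum; 128 per arm are planned, and power there stays above 0.8 across the assumed range with independent controls. Only with equally clustered controls and an ICC near 0.14 does it come down to about 0.8. The 0.70 / 0.63 / 0.57 applies to the printed 64, or to an analysis of the first social-services year alone. Recruitment at the time of writing (42 social-services children, one Junis group started) may limit power more than clustering does, but that is a different matter.

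Other tempting extensions also go beyond the text. The groups are not described as closed, and each is not said to have its own leader; fifteen social-services leaders had been trained, so shared leadership is possible. The primary aim concerns relatives of people with addiction problems, which the Background ties to social services rather than to Junis. Finally, both comparisons are non-randomised, and confounding by setting may well be the larger threat. All of this limits the weight of the point, but it does not make 64 the right figure for children treated in groups.

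**Conclusion.** The point holds in two parts. First, as a matter of arithmetic, 64 per group is the independent-children figure and does not give 80% power when the 64 treated children form eight groups: about 0.70 / 0.63 / 0.57 at an assumed ICC of 0.05 / 0.10 / 0.15. The planned 128 per arm covers this before dropout, so it is a misstated figure rather than a demonstrated shortfall.

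Second, and conditionally, if the matched comparison followed the same independence, its true standard errors would be about 8% / 16% / 23% larger than reported and the 5% test would reject about 7% / 9% / 11% of the time under no effect, more if clustering of controls were ignored as well. Both parts rest on an ICC the protocol does not supply, groups of eight and 1:1 matching. It should be corrected, but it does not undermine the design.

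**What to change.** In Participants and recruitment, restate the figure for these two arms with a design effect of 1 + 7 × ICC over a stated range, for example 0.05 to 0.15, and report the power at the planned 128 per arm alongside it.

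In Data management and analysis, state that the matched comparisons use a random effect for RESCUR group among treated children and for school among controls, with small-sample degrees of freedom. Cluster-robust standard errors by RESCUR group and school, with a small-sample correction, would also serve.

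The cost is one revised power statement and one analysis sentence, plus carrying a RESCUR-group identifier in the data set. No additional children are needed. The downside is wider intervals and a less favourable stated power.

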## Discussion

The protocol of this research project has shown how the planning and development of the research make it feasible to answer the five research questions.How can participants in the implementation of the intervention be recruited? The question is answered by analyzing the interviews with the leaders and researchers developing the methodology and the framework of the study. Analysis of the written documentation that the research group continuously makes during the recruitment work is also important.How can leaders be supported to enable implementation of high quality intervention? This question will be approached through the documentation of the tutorial process as well as the analysis of interviews with teachers and group leaders. The support and supervision of the people implementing the method is of great importance for the results [60, 61].The project can contribute to filling knowledge gaps by implementing the planned intervention in school and in recreational activities, where there are no studies available according to the Swedish Agency for Health Technology Assessment and Assessment of Social Services’ (SBU) review of controlled prevention of child and adolescent abuse [62]. By planning for the long-term follow-up of initiatives, future preventive effects can also be made.What is the importance of the intervention for the development of children and their mental health? Mainly statistical analyses of data from pre- and post-measurements. Analysis of interviews with children and interviews by leaders will complement the statistical analysis.Does the intervention work differently for different groups in relation to gender, social background, place of residence, and age? Comparisons are made between the results of pre- and post-measurements, with child and adult reports for the different groups.Does the intervention work differently at universal, selective and indicated levels? The answer will be based on before and after measurements, with child and adult reports and statistical analyses. Comparisons of effect sizes will be made between the arms of the study (voluntary organization, social services, and school). Analysis of leader interviews and observations will complement these comparisons.

Good measuring instruments are needed to further develop the field of study. In an overview, it was found that there was no gold standard among the 19 scales used for measuring resilience [63]. According to one research group [64], a combined assessment is needed, including assessment of vulnerability (severity, chronic or not, ecological level, child’s perception of causes, as well as cultural and contextual relevance), of resilience (with an individual dimension – personality and thinking, and with a contextual dimension), and of contemporary and cultural aspects. The contextual dimension covers all levels of vulnerability, such as the availability of individual, family, social and political resources. It covers strategic use of biological, emotional, psychological, spiritual, social and political resources. Moreover, the contextual dimension also includes dynamic elements such as positive feedback on individual coping strategies from family and society, and adaptability in the environment to the needs of individuals, families and society [64]. The chosen measure of resilience, the Child and Youth Resilience Measure, is a promising newer tool that has been developed to cope with the challenges to measure resilience in different settings in an age-appropriate way.

As this research deals with children, ethical considerations are of the utmost importance. It is important for this research project to protect both the generation of knowledge [65] and the individual [66]. This means taking consent, confidentiality and utility requirements into account. There are several ethical challenges in the project that have to do with the groups’ vulnerabilities. Researching children means that ethical issues must be clarified. This applies, for example, to access, power and consent [67]. It is also important not only to ask children about their views, but also to make sure their views really count [68]. Research should be done with children instead of just on or about children [69]. Children’s views may differ from what adults think children think [70].

In order to give consent, it is important that children receive very detailed and age-sensitive information, especially about the right to say no to participation [70, 71]. Children and adolescents must be protected in research, which means that the risks of ill-health or injury must be minimized. This means that we need a strategy for how the child or youth will be supported if problems arise [71]. If an individual in the project is under the age of 15, informed consent from a parent is required for participation in the research [72]. In order to comply with research ethics, we will seek active consent from the children before the evaluation starts. After the children have received information about the project and the evaluation, including ethical principles, they can accept or refuse to participate in the evaluation. The child’s response to participation in the research will not affect their participation in the program and how they are treated or responded to otherwise.

The study includes children who are in an exposed situation. Thus, it is extra important to conduct the project so that these children will not be harmed. We will follow all ethical requirements for the implementation of the project. This applies both to the implementation of the method and the evaluation. Well-trained and experienced staff will deliver the method. The work will be carefully monitored through self-assessment forms and observations by the project management team. Conventional working methods for conducting research with children in Sweden will be followed [73]. We take these measures to reduce the risk of children being harmed in any way.

At the same time, it is of the utmost importance that particularly this group of children, who run a high risk of developing their own problems, get interventions that are tested and effective. It is also important that the child’s own perspective is considered. At the same time, it is important to distinguish between children’s perspectives and the perspectives of adults on the child [74].

Our main target group consists of children aged seven to twelve. Because the children are so young we will also obtain active consent from the children’s parents. The main principle is to collect parental consent in writing. In cases where we fail to communicate with the parents by letter, they will be contacted by telephone and asked for their active consent for their children to be included in the study. Thus, we use dual active consent, from both the child and the parent. Both parties must accept study participation for the child to be included in the study. Our secondary target group includes program deliverers, who give active consent.

Implementing this type of research with the highest ethical standards is a key concern, as well as implementing the RESCUR material in an efficient way together with participating children, parents, teachers and group leader. We consider the potential of the project to benefit children in general, and children in vulnerable positions in particular, to be high.
